## Abstract

**Background:**

In addition to academic problems, children with a speciﬁc learning disability (SLD) encounter problems with participation in activities outside school.

**Purpose:**

To investigate the efficacy of Occupational Performance Coaching (OPC) with and without Four Quadrant Model of Facilitated Learning (4QM) in the mothers of children with SLD.

**Method:**

A single-blinded, parallel-group randomized clinical trial will be carried out. Mothers of children with SLD will constitute the participants and be allocated to experimental (OPC+4QM) and control (OPC alone) groups.

**Key issues:**

Children's occupational performance and satisfaction, participation in activities outside school, goals attainment, executive function, and academic achievement along with self-efficacy of mothers will be measured in baseline, post-intervention, and one-month follow-up stages.

**Implications:**

An OPC intervention protocol may improve children's participation in activities outside school and may help clarify whether 4QM promotes maternal empowerment and better results for children with SLD.

**Trial registration:**

Clinical Trials, IRCT20140416017301N9. (https://en.irct.ir/trial/55842)

## Abbreviations

SLDSpeciﬁc Learning DisabilityOPCOccupational Performance Coaching4QMFour Quadrant Model of facilitated learning

## Introduction

1

Specific Learning Disorders (SLD) is a neurodevelopmental disorder characterized with declined academic capability in the early years of elementary school and is two to three times more common in boys than in girls [1]. Children with SLD have a normal intelligence (IQ > 70); however, experience difficulties in reading, writing, speaking, or executive functions [2]. The prevalence of SLD among school-age children is reported 4.58–7% in Iran [3,4] and 5–15% in other countries [1].

Based on the DSM-V (Diagnostic and Statistical Manual of Mental Disorders), the severity of SLD is measured by the extent of participation in occupational performance areas, especially activities outside of school [1,5]. Activities outside school include basic activities daily of living (BADL), instrumental activities daily of living (IADL), play, leisure, social participation, education (except academic functions), work, and sleep/rest [5,6].

Studies show that the neuro-motor developmental deficits in children with SLD have caused limitations in activities outside school such as self-care activities (e.g. shoe tying, buttoning up clothes and getting dressed), productivity activities (e.g. legible writing and doing homework), and leisure activities (e.g. playing with peers and painting) [[7], [8], [9], [10]]. Furthermore, children with SLD often show failure in executive function skills and thus struggle with acquiring new skills in almost every domain of life [[11], [12], [13]]. The extra effort for learning new tasks, such as tying shoe laces or riding a bike, results in avoiding these activities and leads to participation restrictions in activities outside school [8,14]. Unfortunately, only the academic issues have received the attention while there is a significant correlation between academic skills and participation in daily life activities in children with SLD [15]. Based on the Occupational Therapy Practice Framework (OTPF-4th edition), “participation in occupations is a key part of development and life experience for man, which provides the opportunity to gain competencies and skills and find meaning and goal in life” [16]. Therefore, participation in activities outside school is an important indicator of health and well-being that helps to encourage positive development into adulthood and should be considered as a major goal of rehabilitation services [17,18].

Studies have reported defects in executive function domains such as verbal working memory, sequencing [19,20], set-shifting [21], planning, timing [22], and response inhibition [23] in children with SLD. Executive function skills shape various routine and non-routine activities of daily life and also participation in the various areas of occupation [[24], [25], [26]]. Children suffering from executive dysfunction may have deficits in dealing with complicated occupations with dynamic task demands and multiple steps, like IADL and social participation which can lead to restrictions in their life roles [27,28]. Performing unprecedented tasks also creates a challenge for these children as they cannot perform actions they have learned to perform automatically (inhibitory control and cognitive flexibility) for fulfilling new challenging activities in different contexts (transfer and generalization). Therefore, these children are limited in terms of participation in everyday activities [29,30].

The ICF-CY (International Classification of Functioning, Disability, and Health-Child and Youth) as a biopsychosocial framework, indicates that child's performance, health, and wellbeing depend on the dynamic interaction between the activities, structures and body functions, and participation taking into account the personal and the environmental factors [31]. Therefore, facilitating children's participation in activities outside school, in addition to improving body function and structure such as executive functions increase their independence in occupational performance.

Mothers with SLD children spend long hours and a great deal of energy on the education of these children compared to their siblings [32]. Sahu et al. (2018) showed in their exploratory study on the perception of families of SLD children that different supportive strategies are needed to empower mothers of these children [33]. In addition, such services warrant mothers' training to support the learning skills of their child [34]. On the other hand, studies on children with special needs show that the most effective services emphasize the family's role in treatment [35,36]. Therefore, empowering mothers to identify barriers and facilitators of their child's participation in activities outside school and solving their problems through collaboration with a therapist is one of the main priorities of children's rehabilitation, which in turn can strengthen their self-efficacy.

Occupational Performance Coaching (OPC) is a family-centered, occupation-based, solution-focused intervention that directly targets children's participation in activities outside school through working with their mothers as the mediators of change [37,38]. The OPC incorporates three key domains including information exchange, emotional support, and a structured process that mixes performance analysis frameworks of current performance with coaching techniques to involve mothers in goal-specific and collaborative processes. Goals are set through exploring available options in the child (knowledge, motivation, and ability), task (sequence, steps, and standard expected), and environment (physical and social) using collaborative performance analysis (CPA). To explore options includes leading the mother to examine her child's current level of performance, determine the ideal level of performance they would like to happen to her child, and identify bridges, and barriers to the child's success in performance. Eventually, planning and taking action to attain occupational performance goals related to child participation happen in the home and community [38]. Through OPC, mothers learn to develop their problem-solving ability by identifying novel, ambitious, but highly individualized, and directly applied strategies to improve their child's participation in activities outside school [39].

As mentioned, children with SLD have difficulty acquiring new skills of daily life activities [8,9]. Skill learning is a major step in achieving occupational goals that is attained through utilizing learning and teaching as major ways of intervening pediatric practice [40]. According to Vygotsky's theory, children need support to learn the necessary skills and develop their abilities. In other words, progress toward independence and autonomy in performing tasks is made possible through systematic facilitator support [41]. This concept is consistent with the Mosston and Ashworth's study that stated teaching a task is like a spectrum that starts with command-style (teaching key elements directly to the learner along with the way of reacting to task demands) and ends with self-teaching (motivates learners to take into account the challenges to perform the activity and the way of achieving independence and autonomy through decision-making processes) [42]. Thus, selecting effective and systematic teaching-learning strategies based on the body functions of SLD children (e.g. executive functioning), mothers' awareness of learning level, and changing needs of children during the acquisition of new skills seems to help to booster OPC and finally better improve participation in children's activities outside school.

One of the models of learning facilitation in the teaching-learning approach is the *Four Quadrant Model of Facilitated Learning* (4QM), which was first proposed by Gerber in 2007 [43]. The 4QM provides the various systematic physical and cognitive learning strategies needed in guiding children to carry out occupational tasks autonomously and independently [44]. Executive function skills such as initiation, termination, planning, organization, self-monitoring, self-control, working memory, time management, and organization are included in the four quadrants of this model [45]. In quadrant 1, learning strategies are direct, initiated by the mother, and determine the features of the task and/or the performance requirements. The rest of indirect strategies, which are mother-initiated, are in quadrant 2. Such strategies encourage decision-making by the child. Quadrant 3 encourages the child through the use of overt self-prompts to recall key points and finally, quadrant 4 includes a range of self-regulatory metacognitive and cognitive strategies that help the child's autonomy and independence [44]. It is necessary to mention that, the 4QM can be employed only when the children with SLD are judged to have the necessary performance components to complete the activity [43]. In other words, after identifying barriers to achieving the goal (barriers related to the child, activity, and context) through OPC, independence in the goals of participation seems to be facilitated with 4QM.

The OPC is potentially effective through empowering mothers to improve children's participation in various life situations [37,38,46]. On the other hand, adding 4QM as a reinforcement tool to OPC, increases the learning needs of mothers and facilitates teaching necessary skills to children with SLD. The most relevant evidence to this hypothesis is the recent single-subject study of the effectiveness of OPC with 4QM in the occupational performance of six children with SLD [47]. As far as the authors know, there has been no study on rehabilitation interventions to improve participation in children with SLD. Studies are limited to participation patterns and environmental factors [2]. Generally, participation of children with SLD has not received the attention it merits. Thus, the present study explores the use of 4QM, in addition to OPC, in the experimental group and investigates the effect of this intervention on improving the outcomes for children with SLD.

The primary objectives are to examine the efficacy of the OPC approach with and without 4QM on occupational performance, satisfaction, and achievement of goals (transfer and trained goals) and participation in activities outside school for SLD children. In addition, the efficacy of OPC+4QM versus OPC on similar results will be examined. The second-level goals are to examine and compare OPC+4QM and OPC efficacy on executive performance (such as organization, cognitive flexibility, and mental planning); to investigate and compare academic achievement; and to examine and compare self-efficacy in mothers of children with SLD. The trial's hypotheses state that OPC+4QM and OPC are effective in improving outcomes in children and parents and the experimental group submitted to OPC+4QM have better effects on the main and secondary outcomes immediately and one month after the interventions.

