### Sample size

2.4

Sample size calculations were performed in G-Power software based on the COPM test as the main variable of the study. A two points change in this variable between the intervention and control group will be considered as significant difference [49]. Considering α-value of 5%, the power of 95%, the standard Cohen's effect size of 1, the required sample size was obtained equal to 27 for each group, and assuming 10% dropout rate, 30 subjects were selected for each group. Furthermore, since the sample size was calculated based on the primary outcome, the study is anticipated under-powered for addressing secondary outcomes.

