##### Occupational performance and satisfaction

4.2.1.1

The COPM (Canadian Occupational Performance Measure) will be utilized for scoring occupational performance and satisfaction by the mothers of children with SLD. As a semi-structured interview, COPM helps mothers identify their goals. The participant is asked to score performance and satisfaction with selected goals related to activities outside school on a 10-point score (ranging from 1 = not satisfied to 10 = satisfied) [63]. Two-point change or more overtime are considered clinically relevant. Test-retest reliability for COPM is measured for various populations and it varies 0.84 to 0.92 [64]. The content validity of the Persian version of the COPM is (80.95 ± 0.222) [65].

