### Data analysis

5.2

To analyze the first and second objectives, (a) mean and median changes in the satisfaction and occupational performance scores of the first three goals chosen by the mothers from the COPM from baseline (t_1_) to post-intervention (t_2_) and a 1-month follow-up (t_3_); (b) mean and median changes in the scores of the diversity of participation in activities outside school provided by CPAS-P from t_1_ to t_2_ and t_3_; (c) mean and median changes in goal attainment in the scores of the first three goals chosen by the mothers on GAS from t_1_ to t_2_ and t_3_; and (d) mean and median changes on occupational performance and satisfaction and goal attainment in the scores on COPM and GAS on transfer goals (The fourth and fifth goals chosen by the mothers) to analyze the transfer of skills from t_1_ to t_2_ and t_3_ will be used.

To analyze the third and fourth objectives (a) mean and median changes in the total score of executive function on the BRIEF from t_1_ to t_2_ and t_3_; (b) mean and median variations in educational status on the transcript from t_1_ to t_2_ and t_3_; and (c) mean and median variations in the self-efficacy of mothers on the SGSES from t_1_ to t_2_ and t_3_ will be used.

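### The sample size is built on one undefined COPM outcome, while the protocol makes seven scores primary and ranks none of them

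*Protocol article*

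**What the plan says.** The Introduction gives as primary objectives "occupational performance, satisfaction, and achievement of goals (transfer and trained goals) and participation in activities outside school for SLD children". It expects the OPC+4QM arm to show "better effects on the main and secondary outcomes immediately and one month after the interventions". Section 4.2.1 places four headings under the primary outcome: COPM, GAS, CPAS-P and transfer of skills.

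Section 5.2 makes these operational, each from t1 to t2 and t3:

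- "mean and median changes in the satisfaction and occupational performance scores of the first three goals chosen by the mothers from the COPM" (two scores);
- "mean and median changes in the scores of the diversity of participation in activities outside school provided by CPAS-P" (one score);
- "mean and median changes in goal attainment in the scores of the first three goals chosen by the mothers on GAS" (one score);
- COPM performance, COPM satisfaction and GAS again, on the two transfer goals (three scores).

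Section 2.4 speaks of one primary outcome: "Sample size calculations were performed in G-Power software based on the COPM test as the main variable of the study". Its target is stated thus: "A two points change in this variable between the intervention and control group will be considered as significant difference". Section 4.2.1.1 gives the same number for another quantity: "Two-point change or more overtime are considered clinically relevant".

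Section 5.3 applies ANOVA to all primary and secondary results, with time and group interactions in the models and a single p threshold. The article states no ranking among the primary measures.

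**The concern.** Sections 1, 4.2.1 and 5.2 treat several measures as primary, and section 2.4 treats one. The COPM alone does not identify that one. It yields 2 scores on 2 goal sets at 2 post-baseline times, which is 2 × 2 × 2 = 8 possible contrasts between arms. Section 2.4 admits low power only for secondary outcomes, so a reader would take all the primary measures to be powered at 95%.

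Two things are at stake. With no named endpoint, a positive result can be selected afterwards from seven primary scores. And the power statement is hard to interpret, because the comparator is active: both arms receive OPC, which the protocol itself expects to help. A 2-point difference between arms is then a 2-point gain on top of whatever OPC achieves. Section 2.4 gives neither a justification in the text nor an SD for that difference.

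**Working it through.** **Inputs.** From section 2.4: alpha 5%, power 95%, d = 1, a 2-point difference, 27 per group, 10% dropout, 30 per group. From section 5.3: two-sided tests. That section prints the threshold as 0.5; this is a separate point, and the 5% of section 2.4 is used here.

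**1. The plan's own figure.** For a two-sided two-sample t-test, power = 1 − F(c; df, λ) + F(−c; df, λ). F is the noncentral t distribution, df = 2n − 2, λ = d√(n/2), and c is the 97.5% point of t.

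- n = 27: df = 52, λ = √13.5 = 3.67, power 0.950.
- n = 26: power 0.942.

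So 27 is the smallest n that reaches 95%, and 27/0.9 = 30. The arithmetic is right.

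**2. Number of primary scores.** Three scores (COPM performance, COPM satisfaction, GAS) × 2 goal sets + CPAS-P = 7.

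**3. False-positive risk, if any one score can carry the claim at 5%.** Under independence it is 1 − 0.95^m. The correlated values come from simulating equally correlated normal test statistics; the correlations are assumptions.

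| Tests | Independent | Correlation 0.5 | Correlation 0.8 |
|---|---|---|---|
| 7 (one per score) | 1 − 0.95^7 = 30% | 23% | 15% |
| 14 (t2 and t3 tested separately) | 1 − 0.95^14 = 51% | 35% | 20% |

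**4. Power at d = 1 with 27 per arm if alpha is shared (Bonferroni).**

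- One test at 0.05: 95%.
- Seven tests at 0.05/7 = 0.00714: 80%.
- Fourteen tests at 0.05/14 = 0.00357: 73%.

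**5. Differences smaller than 2 points.** The SD is not stated; 2 points at d = 1 imply SD = 2/1 = 2. Power with 27 per arm, over an assumed range of SD:

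| Difference between arms | SD 1.5 | SD 2 | SD 2.5 |
|---|---|---|---|
| 1 point | 67% | 44% | 30% |
| 1.5 points | 95% | 77% | 58% |
| 2 points | 99.8% | 95% | 82% |

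At 27 per arm, d = 0.777 gives 80% power. In points this is 0.777 × 2 = 1.55, with a range from 0.777 × 1.5 = 1.17 to 0.777 × 2.5 = 1.94.

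**The case against.** The strongest reply is that multiplicity rules commonly sit in an analysis plan, which is not shown, and that this is a condensed article. That stands in part: nobody can infer from it that the trial has no error control. It does not answer the point, because an adjustment rule elsewhere would not settle which outcome section 2.4 means, and the article's own sections disagree on that.

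Three further objections limit the size of the point.

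- **Number of tests.** A reader might count 14, because the hypothesis names two time points. Section 5.3 describes models with time and group interactions, which fits one interaction test per score. Seven is the count the text supports; the 14-test figures are conditional.
- **Success rule.** The error rates assume that any one score suffices. The article states no such rule. If the hypothesis means superiority on every outcome, alpha is not inflated and the difficulty becomes power. Independence is also the least plausible case, since the scores share instruments and mostly come from the same mothers.
- **Origin of the 2 points.** A reader might infer that the threshold for change over time in section 4.2.1.1 was carried over as the difference between arms. The documents do not show this: section 2.4 cites a source that is not available here, and it expressly describes a difference between groups. A target of this size is an optimistic assumption against active OPC, not a demonstrated error.

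**Conclusion.** The point holds as an inconsistency within the protocol. Seven scores are primary in the objectives, the outcome section and the data analysis section, while the sample size rests on one COPM outcome with no score, goal set or time point. The 95% power is correct for one score at one time at full alpha and d = 1, but it is attached to no defined endpoint. Shared over seven scores it is 80%.

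Under an any-one-suffices rule at 5%, the false-positive risk is 15% to 30% for correlations from 0.8 to zero, and higher (20% to 51%) only if t2 and t3 are tested separately.

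The matter of the 2-point difference is one of reporting: the assumption and its SD should be stated. The 44% and 1.55-point figures rest on a back-calculated SD of 2 and should be read with their ranges. Nothing here shows that 27 or 30 per group was miscalculated.

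**What to change.** 1. In sections 2.4 and 4.2.1, name one primary endpoint consistent with the COPM as the main variable: score, goal set, time point and contrast between arms. One example is mean COPM performance over the three trained goals at t2. The documents do not favour performance over satisfaction or t2 over t3, so the choice is the sponsor's, to be made before unblinding.
2. Make the other six scores and the other time point secondary with Holm adjustment, or label them exploratory.
3. Limit the 95% power statement to the named endpoint.
4. In section 2.4, state that 2 points is an assumed difference between OPC+4QM and active OPC, distinct from the change over time in section 4.2.1.1. Give the assumed SD, and report the 80%-power detectable difference (1.55 points; 1.17 to 1.94 for SD 1.5 to 2.5) and the power at 1 point (44%; 67% to 30%).

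The cost is wording. The other measures, including participation outside school, lose primary status, and the power statement reads less favourably. The sample size stays at 27, or 30 with dropout, per group. Keeping all seven scores primary under a Bonferroni split would instead need 40 per group for 95% power at d = 1, or 40/0.9, rounded up to 45, with dropout.

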### Design and setting

2.1

The study will be a single-blinded, parallel-group, and randomized clinical trial with an add-on component. The OPC model will be implemented for all participating mothers. Four extra training sessions of 4QM will be provided to mothers in the experimental group. The Ethics Committee of the Iran University of Medical Sciences, Tehran, Iran (IR.IUMS.REC.1400.060) approved the study. It was also registered as a randomized controlled trial (IRCT20140416017301N9) at http://www.irct.ir/.

The study place will be the centers for special learning problems affiliated with Exceptional Education in Tehran. The first author ([name]) will be responsible for the study processes. He is a clinician with experience and an occupational therapist and has experience working with mothers on OPC and 4QM interventions.

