## Interventions

3

First, necessary explanations about the importance of OPC or OPC+4QM for participation in outside school activities in SLD children will be given to the mothers. To ensure adherence and compliance to treatment, an evaluation form to assess mothers' ability to implement the instruction of each session and important issues during the intervention course will be completed by each participant. Mothers will not be required to quit other interventions, if any, such as psychology or their child's school tutorials; however, they need to avoid engaging in other occupational therapy interventions.

Second, the original OPC (Graham & Rodger, 2010) and 4QM (Greber, 2007) protocols will be used in the study groups [39,50]. Two occupational therapists who have more than 5 years of experience working with mothers with children with neurodevelopmental disorders will conduct the interventions, and both OPC and 4QM protocols are available through manuals. A rater will be present during the intervention sessions in both experimental (OPC+4QM) and control (OPC) groups and complete the occupational performance fidelity measure (OPC-FM) to observe the principles of OPC by the therapist and also to check the quality of behavior of the mothers [[51], [52]]. OPC-FM consists of 18 items, and a higher score indicates a better OPC behavior. The average score will be 34.1/45 for the first session and 41.3/54 for the other sessions. The minimum requirement recommended in the coaching manual will be 80% fidelity in every session [51].

Third, all the participating mothers will be provided with a booklet for the study based on prior experiences containing information related to OPC and an additional part about implementing the 4QM approach and guided discovery to help the improvement of participation in activities outside school-related to their children.

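### A primary objective and hypothesis claim that OPC and OPC+4QM each work, but every mother receives OPC, so the design can test only what 4QM adds

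*Protocol article*

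**What the plan says.** The last paragraph of the Introduction sets two separate primary aims. The first: "The primary objectives are to examine the efficacy of the OPC approach with and without 4QM on occupational performance, satisfaction, and achievement of goals", extended to participation outside school. The second follows as an addition: "In addition, the efficacy of OPC+4QM versus OPC on similar results will be examined". The hypothesis has the same two parts. It states that "OPC+4QM and OPC are effective in improving outcomes in children and parents", and then that the experimental group does better. The Purpose in the Abstract also speaks of the efficacy of OPC with and without 4QM.

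The design has two arms. Mothers will "be allocated to experimental (OPC+4QM) and control (OPC alone) groups" (Abstract, Method). Section 2.1 states that "The OPC model will be implemented for all participating mothers" and that "Four extra training sessions of 4QM will be provided to mothers in the experimental group". No waiting-list, usual-care or attention arm is described.

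Section 5.2 assigns mean and median changes from t1 to t2 and t3 to the first and second objectives. Section 5.3 names ANOVA for comparing OPC+4QM with OPC and mentions multivariate models with time and group interactions. Section 2.4 powers only the difference between the two arms.

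**The concern.** Randomisation protects only a contrast between randomised groups. Here the groups differ by the four 4QM sessions, so the trial can estimate what those sessions add to OPC. Whether OPC works, or whether the OPC+4QM package works compared with no coaching, needs a group without OPC. Without one, the first aim can be addressed only by change within an arm, and the protocol itself supplies other explanations for such change:

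- Mothers choose the goals as priority worries about the child (sections 3.1 and 3.3), so low starting scores will tend to rise on re-rating.
- OPC runs for ten weekly sessions with a one-month follow-up (section 3.1), while school-age children mature and are taught.
- "Mothers will not be required to quit other interventions, if any" (section 3), with psychology and school tutorials given as examples.
- Mothers score the COPM (section 4.2.1.1) and are not blinded (section 2.6).

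At stake is a primary conclusion. An improvement over time could be read as confirming the first hypothesis although nothing in the design separates it from these influences.

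**Working it through.** **1. What each contrast can identify.**

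| Stated aim (Introduction) | Comparator in the design | What the data can show |
|---|---|---|
| OPC is effective | none; the control arm is OPC alone | change from t1 in the OPC arm, uncontrolled |
| OPC+4QM is effective | none without OPC | change from t1 in the experimental arm, uncontrolled |
| OPC+4QM is better than OPC | randomised OPC arm | effect of adding the four 4QM sessions |

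Only the third row is protected by randomisation.

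**2. Do the transfer goals supply a control?** Section 4.2.1.4 says that the fourth and fifth goals are not covered in the intervention, but it defines them as outcomes measuring transfer. Section 3.1 has mothers implement them during follow-up, so by t3 they are no longer untreated. Even at t2, Table 1 lists generalisation among the facilitating actions of OPC, so they are not expected to stay free of its effect.

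**3. The plan's own figure.** Section 2.4 gives a 2-point COPM difference between groups, Cohen's d = 1, alpha 5% and power 95%. A two-sample t test, two-sided as in section 5.3, needs 26.99, so 27 per group. With 10% dropout, 27 / 0.90 = 30. The stated numbers reproduce, and they belong to the between-arm contrast only.

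**4. Length of exposure in the OPC arm.** Ten weekly sessions take about 10 weeks to t2. One further month gives about 14 weeks to t3.

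**5. Illustration of a within-arm test when OPC has no effect.** Suppose scores rise by m points for reasons other than OPC, and the SD of change is s. A one-sample t test on n = 27 has noncentrality (m / s) × √27, 26 degrees of freedom and a two-sided 5% critical value of 2.056. Section 2.4 implies an SD of 2 / 1 = 2 points without saying whether it is of scores or of changes, so s is varied. Both m and s are assumptions.

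| Rise m | SD of change s | (m / s) × √27 | Probability of p < 0.05 |
|---|---|---|---|
| 1 | 3 | 1.73 | about 39% |
| 1 | 2.5 | 2.08 | 52% |
| 1 | 2 | 2.60 | 71% |
| 1 | 1.5 | 3.46 | 92% |
| 0.5 | 2 | 1.30 | 24% |

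In every row the probability is well above 5%, although OPC is assumed to do nothing.

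**The case against.** The best defence is that the plan never specifies a within-arm efficacy test. Section 5.3 ties ANOVA to OPC+4QM versus OPC, section 2.4 powers only that, and the changes in section 5.2 are close to descriptive reporting. This stands. A reader might infer that a significant time effect will be reported as proof that OPC works, but the document does not say so. Because the models include time, a time effect could be tested and over-read; that is a risk, not a stated plan.

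A reader might also infer that the article's conclusions overclaim. They do not: the Implications in the Abstract and the Key messages say only that OPC may improve participation.

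The rival explanations have limits. Mothers must avoid other occupational therapy, the closest competing intervention. Study hypotheses are withheld from them, and school grades come from the teacher. Unblinded maternal rating affects the randomised contrast too, so it is not peculiar to the first aim. A period of 18 weeks would apply only to the experimental arm, and only if its fourteen weekly sessions ran consecutively; section 3.2 also places the 4QM sessions during the OPC sessions.

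Finally, the illustration describes any uncontrolled before-after test and measures nothing particular to this trial. That is fair, and it carries no weight beyond illustration.

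None of this supplies a comparator. The conflict lies between a stated primary objective and the stated design, so a fuller analysis plan could not resolve it.

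**Conclusion.** The point holds for the objective and hypothesis in the Introduction, echoed in the Purpose of the Abstract. The aim to "examine the efficacy of the OPC approach with and without 4QM on occupational performance" cannot be met as a claim of efficacy, because both arms receive OPC and each arm's own effect rests on uncontrolled change. This follows from the design and depends on no figure.

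The size is illustrative only. A 1-point non-specific rise in an arm of 27 gives a significant within-arm result in about 39% to 92% of trials for an SD of change from 3 down to 1.5, with both quantities assumed.

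The stronger reading, that the trial is invalid or its sample size wrong, is not supported. The randomised comparison of OPC+4QM with OPC and its 27 (30) per group stand.

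**What to change.** - In the Introduction, make OPC+4QM versus OPC the sole confirmatory objective and hypothesis, and align the Purpose in the Abstract.
- In section 5.3, state that this objective is tested by the group or group-by-time effect.
- In section 5.2, label changes from t1 to t2 and from t1 to t3 within each arm, and any time effect, as descriptive, and report them with confidence intervals.
- State that the trial cannot establish the efficacy of OPC itself, and that the transfer goals are outcomes and not a control.
- The Implications in the Abstract and the Key messages need at most light alignment.

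The cost is more modest claims. As the trial has ethics approval and is registered, a wording amendment to the protocol and the registry entry is probably needed. Sample size, visits and measures do not change.

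Keeping efficacy of OPC as a confirmatory aim would require a concurrent arm without OPC. At the same d = 1 and unadjusted alpha, which is an assumption for that contrast, this means 3 × 27 = 81 mothers, or 3 × 30 = 90 with dropout, instead of 60.
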